#### Randomisation

People with MS will be assigned to occupational therapists, based on geographic location, and the occupational therapists will be randomly assigned to one of two study arms (i.e. COB-MS delivery or wait-list control), using 1:1 allocation, via randomised block permutation. Notably, cluster randomisation was the most appropriate randomisation strategy for this trial, given the potential for contamination in an individually randomised trial. A web-based clinical trial randomisation service will be used (Sealed Envelope). An independent, unblinded researcher will conduct the randomisation, having been provided information regarding sequence and type of randomisation to be used (as described above) by the statistician (who is not involved in participant allocation). Participants will be informed of their allocation by an unblinded research assistant, through post and phone call. Participants’ details will be passed to their allocated occupational therapists to initiate contact and the intervention.

#### Inclusion and exclusion criteria

Occupational therapists will be eligible to participate if they meet the following inclusion criteria for the study: (1) currently working in Ireland as an occupational therapist; (2) registered with Health and Social Care Professionals Council, Ireland; (3) have experience working with people with MS; and (4) can commit to the requirements of the study. Though there are no exclusion criteria for occupational therapists (apart from not meeting the inclusion criteria), if more occupational therapists express an interest in participating than are required, selection criteria will be applied to prioritise occupational therapists based on: (1) geographic proximity to participants with MS; (2) experience of conducting group-based interventions; and (3) experience working with those with cognitive difficulties.

People with MS will be eligible to participate if they meet the following inclusion criteria for the study:Aged 18 years of age or olderFluent in written and spoken EnglishHave a diagnosis of multiple sclerosis (consistent with the McDonald Criteria for the Diagnosis of Multiple Sclerosis [29])Cognitive difficulties, as shown by a score of > 22 on the Multiple Sclerosis Neuropsychological Screening Questionnaire (MSNQ) [30]Are clinically stable (i.e. not having an active relapse)Can provide informed consentNo neurologic history other than MS, including evidence of current dementiaNo history of major depressive disorder, schizophrenia or bipolar disorder I or IINo history of diagnosed substance use or dependence disorderNot currently undergoing any other form of cognitive rehabilitationLiving in the community.

The exclusion criteria for people with MS are: (1) cognitive impairment that would affect reliable participation or capacity to give informed consent; (2) being incarcerated or institutionalised; and (3) significant neurological condition or organic brain damage (unrelated to MS).

### Measures

#### Primary outcome

*Goal attainment scaling* [31] allows participants to set meaningful goals relating to daily life which can be measured in a systematic way. This technique has shown excellent inter-rater reliability (*r* = 0.95) and construct validity (*r* = 0.92) in cognitive rehabilitation [32]. Goal attainment scaling shows reliability, validity and sensitivity when utilised within a population of adults and older people [33]. The primary endpoint will be at the 12 weeks follow-up.

#### Secondary outcomes

Various tests and measures are used to evaluate the secondary outcomes. They are listed as follows:*Symbol Digit Modalities Test (SDMT)* [34]. Within the *Minimal Assessment of Cognitive Function in Multiple Sclerosis (MACFIMS)* [35], the SDMT appears to be the strongest predictor of future cognitive decline, thus supporting its sensitivity and construct validity [36]. Similarly, a meta-analysis [37] found the SDMT to have the strongest correlation (*r* = 0.71) with several assessments of processing speed. Research has shown excellent test-retest reliability (*r* = 0.97) at 2-week [38] and 4-week [39] retest intervals for individuals with MS.*California Verbal Learning Test II (CVLT-II)* [40]. The CVLT-II is part of the MACFIMS [35], an established battery of assessments on the fundamental domains of cognition to be assessed in MS. The inter-rater reliability of the CVLT-II ranges from 0.80 to 0.96 [40]. Correlation coefficients for the CVLT-II and CVLT in recall and learning variables range from 0.72 to 0.80, supporting its construct validity [40].*Trail Making Test (TMT)* [41]. The TMT has excellent construct validity, with correlation coefficients ranging from 0.73 to 0.90 with other measures such as the Wechsler Adult Intelligence Scale – III [42, 43]. Inter-rater reliability for the TMT is also high, *r* = 0.96 [44].*Brief Visuospatial Memory Test-Revised (BVMT-R)* [45]. Similar to the CVLT-II, the BVMT-R is part of the MACFIMS. The inter-rater reliability of the BVMT-R ranges from 0.96 to 0.97, and test-retest reliability coefficients range from 0.60 to 0.84 [45].*Everyday Memory Questionnaire-Revised (EMQ-R)* [46]. Research by the authors revealed a Cronbach’s alpha of 0.91 for the EMQ, showing good internal reliability. Strong discriminatory properties were also evident between the neurological and control groups. The researchers then examined the correlations between the EMQ and the EMQ-R, and found that both measures were highly correlated (MS *r* = 0.98; stroke *r* = 0.94; healthy control *r* = 0.97), supporting the EMQ-R as a reliable and valid measure for use in a population of MS.*Everyday Memory Questionnaire Revised-Relative* [46]. Participants will be given the option of having a family member complete the EMQ-R to provide a proxy rating of function and potential change. This was added as an optional measure based on public and patient consultation.*Generalised Self-Efficacy Scale (GSES)* [47]. The GSES aims to predict participants’ ability to cope with daily difficulties and adaptation to any stressful life events [48]. Cronbach’s alphas ranged from .76 to .90 across 23 countries, with the majority in the high .80s.*Modified Fatigue Impact Scale* [49]. This scale is a self-report measure of the impact of fatigue on the participant’s life. It examines physical, cognitive and psychosocial impacts of fatigue. It has a Cronbach’s alpha of .81 and discriminates between fatigue seen in MS and that seen in other conditions.*Multiple Sclerosis Quality of Life-54* [50]. This instrument measures health-related quality of life via 54 generic MS-specific items. It has population-based normative data available and both good internal validity and test-retest reliability.*General Health Questionnaire-12 (GHQ-12)* [51]. The GHQ-12 is a well-validated and standardised 12-item measure of general levels of distress, which can utilise a 4-point Likert score, with higher scores on the scale indicating higher distress. The GHQ is among the most treatment-responsive measures of psychological distress in MS [52, 53].

#### Screening

The Multiple Sclerosis Neuropsychological Screening Questionnaire [30] is a self-report measure, consisting of 15 items that assess cognitive functioning during daily activities in people with MS, regarding various domains, including attention, processing speed and memory. The MSNQ will be administered as a screen for eligibility. The inclusion criterion for cognitive difficulties will be determined in part by a score of > 22 on the MSNQ.

#### Demographic and clinical information

Participants will be asked to provide details regarding their age, gender, nationality, residence, education and health, as well as occupational and marital status. These details will be used for the purposes of correlational analysis and interpretation of the clinical data. Furthermore, programme attendance (i.e. 0–8) and home-based review activity completion (i.e. 0–7) will be assessed to examine programme adherence and engagement. Moreover, acceptability of measures will be rated by participants, and rates of recruitment, consent and retention will also be analysed and evaluated.

#### Programme and occupational therapist rating

Participants will be asked to rate the acceptability of each COB-MS session, as part of their home-based review activities, on a weekly basis. At the end of the COB-MS programme, participants will also be asked to rate their occupational therapists, via a 6-point Likert scale, on six areas relevant to the delivery of the intervention, as a means of controlling for occupational therapist performance. These results will be anonymous, the data will be pooled and the occupational therapists will be aware of this in advance.

### Interventions

#### COB-MS (experimental) condition

COB-MS is a personalised, patient-centred, occupational therapy-based cognitive rehabilitation intervention aimed at improving daily life functioning for people with MS who are experiencing cognitive difficulties. The programme consists of eight sessions (two individual and six group-based), over a 9-week period. COB-MS focuses on goal setting and attainment through managing the demands of employment and daily life via education, remediation and adaptation, using compensatory strategies and routines that can be integrated into daily contexts, while recognising the impact of emotion, motivation and other non-cognitive functions. Session-by-session content details are outlined in Table 1.

**Table 1 Tab1:** Overview of COB-MS [22]

Session, week and format	Summary of COB-MS content
Session 1, week 1, individual	***Focus on You*** • Initial meeting with the occupational therapist with briefing on what will be involved in the COB-MS • Goal-setting with the person with MS on occupations that they wish to target
Session 2, week 2, group	***You and Your Cognition*** • Session will deal with education on the brain and the different areas of cognition • Discussion on how MS can impact cognition and commonly affected areas: memory, information processing, attention, problem-solving and new learning • Some discussion on the impact of cognitive difficulties on day-to-day occupations
Session 3, week 3, group	***You, the Centrepiece*** • How the cognitive difficulties affect you • What changes can be made by you as a person • What can we learn that can help? • Examples include internal strategies, challenging negative thinking, getting organised, using a mental blackboard, improving sleep, managing stress and mood
Session 4, week 4, group	***You, the Person*** • What changes can be made by you as a person • What can we learn that can help? • Further exploration of strategies
Session 5, week 5, group	***Your Environment*** • How does the environment impact cognition? • What can we change that might help? • Examples include external memory strategies, using bullet points, managing distraction, seeking help, managing and prioritising your workload/household duties, exercise, impact of other factors on cognition
Session 6, week 6, group	***Focus on Doing*** • How are our occupations and daily life affected? • What we can do to help: integrate what has been covered to date and strategies that might be helpful • Give clear examples of how to adapt or remediate occupations
Session 7, week 7, group	***Seeking New Challenges*** • Seeking new challenges • Setting goals for yourself • Keeping motivated, maintaining progress and adapting • Group conclusion and debrief
Session 8, week 9, individual	***Testing the Application*** • Review goals and strategies used • Set new goals if appropriate, plan for future • Signpost to groups and services • Debrief and summary

COB-MS will primarily be conducted in a community setting (e.g. occupational therapist’s practice or local community centre), though two individual sessions will be conducted in the participants’ own homes (or a convenient location). In total, the COB-MS group will receive approximately 2 h of one-on-one occupational therapy as well as approximately 6 h of group-based occupational therapy focused on cognitive rehabilitation. Each group session consists of a theory/background discussion regarding different aspects of cognition (≈ 10 min), related strategies (≈ 15 min), application to participants’ own life and goals (≈ 20 min) as well as opportunities to practice such evidence-based strategies (≈ 15 min). Session 1 involves an initial visit with an occupational therapist who introduces the programme and helps the participant set personal goals.

Sessions 2–7 are once-weekly group sessions with a small group (i.e. seven to nine participants with MS). Session 8 is a final, individual session that takes place 2 weeks after the last group session. Acceptability interviews (not part of the treatment) will take place within 2 weeks of intervention completion in order to control for cognitive difficulties affecting recall.

People with MS will be provided with a participant handbook (125 pages in length) that includes programme content with each session summarised, as well as space for in-group and home-based review activities. At the end of the intervention, participants can keep the handbooks and are encouraged to review them regularly. Qualified occupational therapists will receive COB-MS training and will be provided with a facilitator handbook, as well as access to an interactive, resource-infused companion website and ongoing supervision by phone, email or in person at their workplace, if requested (e.g. session-specific supervision). A sample of two COB-MS sessions, per occupational therapist, will be audio-recorded and compared for intervention fidelity, with permission from the occupational therapists. In order to reduce the chance of contamination, occupational therapists will be asked to declare that they will not share their knowledge or the manual/resources with non-trained occupational therapists and will not use COB-MS methods outside of the trial.

#### Control condition

Participants randomised to the treatment as usual, wait-list control arm of the study will not receive the COB-MS during the trial, but will be provided the programme at the end of the data collection period. They will receive standard clinical care. They will be contacted by an unblinded research assistant to explain that they have been allocated to the wait-list control group. Controls will be assessed at the same time points as the intervention arm.

Because services available to people with MS vary, we will be recording occupational therapy and cognitive interventions received by participants during the study period. We will also gather data on the national picture for cognitive interventions in MS. See Fig. 2 for the schedule of enrolment, interventions and assessment.

**Fig. 2 Fig2:**
[figure not shown]
Standard Protocol Items: Recommendations for Interventional Trials (SPIRIT) figure for the schedule of enrolment, interventions and assessment

#### Fidelity assessment

Fidelity will be assessed to ensure adherence to the COB-MS intervention delivery. Recommendations from the National Institute of Health Behaviour Change Consortium [54] will be used as a framework to increase fidelity in five domains: Study Design, Training, Delivery, Receipt, Enactment. Strategies that will be used include training occupational therapists in a standardised way as well as supporting them throughout the intervention delivery, providing occupational therapists and participants with MS with a handbook that details the content of the intervention. A record of the sessions will be kept by occupational therapists, and participants with MS will record their experiences of each session. Occupational therapists will keep a record of the intervention session content, length and other important information after each session, including attendance and home activity adherence. Two sessions per occupational therapist will be recorded to ensure adherence to the COB-MS programme. Feedback will also be collected through interviews and focus groups with the occupational therapists and participants with MS. Maintaining high levels of treatment fidelity will be a key focus in this feasibility trial [55], so we can be confident about the reliability of the results that come from the trial [56].

### Statistical analysis

Data analysis and reporting will follow 2010 CONSORT guidelines. The feasibility outcomes, recruitment rate, acceptability of COB-MS, rate of unblinding, retention rate and randomisation methods will be reported descriptively and narratively. Analysis will take place once all data have been collected. Means and standard deviations (or medians and interquartile range [IQR] as appropriate) will be used for continuous variables, and counts and percentages for categorical outcomes. The retention rate will be estimated using a 95% confidence interval (CI). Estimates (mean and standard deviations) of the primary outcome variable (i.e. goal attainment scaling), at week 12, will inform sample size calculations of a future definitive trial. Data resulting from primary and secondary outcome measures will be evaluated, per protocol, in terms of preliminary efficacy through a series of 2 (condition) × 4 (time) mixed (multivariate) analyses of variance as well as through correlational analysis. No analysis of health economics or cost-effectiveness will take place in this feasibility study.

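### The only analysis set the article names for the efficacy comparison is an undefined per protocol; read as a population, it puts the randomised comparison at risk of selection bias

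*Protocol article*

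**What the plan says.** The Statistical analysis section fixes the efficacy evaluation in one sentence: "Data resulting from primary and secondary outcome measures will be evaluated, per protocol, in terms of preliminary efficacy", carried out "through a series of 2 (condition) × 4 (time) mixed (multivariate) analyses of variance" and correlational analysis. No per-protocol population is defined there or elsewhere, and no as-randomised or intention-to-treat set is named. The same section makes a general commitment, "Data analysis and reporting will follow 2010 CONSORT guidelines", without saying which participants are analysed.

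Three other statements bear on the point:

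- Under Demographic and clinical information, "programme attendance (i.e. 0–8) and home-based review activity completion (i.e. 0–7) will be assessed to examine programme adherence and engagement". No threshold is attached to either count.
- Under Control condition, wait-list participants "will not receive the COB-MS during the trial, but will be provided the programme at the end of the data collection period". For participants generally, "we will be recording occupational therapy and cognitive interventions received by participants during the study period".
- In Statistical analysis, the mean and standard deviation of goal attainment scaling, "at week 12, will inform sample size calculations of a future definitive trial".

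**The concern.** The second objective under Aims and objectives is a comparison with treatment as usual, and it rests on randomising occupational therapists 1:1. In a statistical section, next to a statement about efficacy, most analysts will read per protocol as the population to be analysed. The participant-level adherence data that the article describes are session attendance and home activities, and these exist only for people offered the programme. A set built on them would remove the less engaged COB-MS participants and keep their counterparts among the controls. Engagement may well be related to attaining self-set goals, which is what the primary outcome measures, so the two groups would no longer be comparable.

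The efficacy result is preliminary, but the article gives it weight. Outcomes are among the key risk areas in Progression criteria, and the Discussion foresees immediate clinical use if the programme is effective. This is a choice written into the article, not a detail left to a later document: an analysis plan that followed the sentence would carry the choice forward.

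**Working it through.** **1. Does any stated figure depend on the analysis set?** From Sample size: 90 participants, retention 91%, 95% CI width 13%, 8 per cluster, ICC 0.05.

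- CI width at n = 90: 11.8% (Wald), 12.1% (Wilson), 12.8% (exact, 82/90). The exact width rounds to the stated 13%.
- Design effect: 1 + (8 − 1) × 0.05 = 1.35, and 90 × 1.35 = 121.5 (stated as 121). 121/8 = 15.1, taken as 15 therapists, and 15 × 8 = 120.

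The plan's figures reproduce. They rest on retention, so changing the efficacy set leaves N at 120.

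**2. Who could fail an adherence criterion?** Attendance (0–8) and home activities (0–7) are COB-MS counts. Controls get no COB-MS during data collection, so programme adherence can be failed in one arm only. Other deviations, such as outside cognitive interventions or ineligibility, can occur in both.

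**3. Illustrative size.** The article gives no exclusion rule, adherence rate or adherence–outcome correlation, so the following are assumptions: true effect zero; higher outcome is better; adherence propensity and outcome bivariate normal with correlation r; the least adherent part of the COB-MS arm removed so that a fraction q stays; all controls kept. With φ the standard normal density and c = z(1 − q) the cut-point:

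bias in SD units = r × λ, where λ = φ(c)/q

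- q = 0.9, r = 0.2: λ = 0.195, bias = 0.039
- q = 0.8, r = 0.3: λ = 0.350, bias = 0.105
- q = 0.7, r = 0.5: λ = 0.497, bias = 0.248

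A wider grid:

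| Fraction kept, q | r = −0.3 | r = 0 | r = 0.3 | r = 0.5 |
|---|---|---|---|---|
| 0.9 | −0.058 | 0 | 0.058 | 0.097 |
| 0.8 | −0.105 | 0 | 0.105 | 0.175 |
| 0.7 | −0.149 | 0 | 0.149 | 0.248 |
| 0.6 | −0.193 | 0 | 0.193 | 0.322 |

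**4. Against the precision of the trial.** Take 60 per arm (120/2) and design effect 1.35. The outcome variance among those kept is v = 1 − r² + r²(1 + cλ − λ²), and SE = √[1.35 × (v/(60q) + 1/60)].

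- q = 0.8, r = 0.3: v = 0.963, SE = 0.223 SD. The bias is 0.105/0.223 = 0.47 standard errors, and a nominal 5% two-sided test rejects in 7.6% of trials.
- q = 0.7, r = 0.5: v = 0.873, SE = 0.225 SD. The bias is 0.248/0.225 = 1.10 standard errors, and rejection is 19.7%.

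**5. Effect on a carried-forward SD.** In these two cases the COB-MS SD is multiplied by √0.963 = 0.981 and √0.873 = 0.934, a fall of about 2% and 7%. If the week-12 estimates came from such a set, the mean would be shifted and the SD somewhat reduced.

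**The case against.** The strongest answer is that the article excludes nobody. It sets no attendance threshold, and it states the purpose of the counts: they "will be assessed to examine programme adherence and engagement". The phrase per protocol stands between commas and can be read as in accordance with this protocol; on that reading no one is dropped and the bias is zero. This stands in part. A reader might infer that low attenders will be removed, but no such rule is written. The plain-language reading adds almost nothing to a sentence that is itself part of a protocol, so the analysis-set reading is the more natural one, though not certain.

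Second, a reader might infer that exclusions must fall on COB-MS alone. The article does not support that: outside interventions are recorded for participants generally, and a control who received one or proved ineligible could also leave a per-protocol set. This stands as a correction to the direction and size of any bias. It does not remove the problem, because exclusions for different reasons in the two arms would not restore comparability.

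Third, the exclusion fractions and correlations are all assumed, and the sign follows the sign of r. That stands in full.

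Fourth, the sentence on week-12 estimates does not itself say per protocol, so distortion of those inputs is conditional on their coming from the same set.

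Finally, this is a feasibility trial, and set definitions are often left to an analysis plan. The absence of an intention-to-treat statement is therefore not an error by itself. What can be challenged is the phrase that is there.

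**Conclusion.** The point holds as a defect of wording with a real risk attached. The sole stated efficacy set is an undefined per protocol. If it denotes a population, the main efficacy comparison is open to selection bias, most plausibly towards COB-MS. It would go too far to say that the estimate is biased in that direction: the article supplies neither the rule nor the rates that would settle it. The range of about 0.04 to 0.25 SD rests on 10% to 30% one-sided exclusion and a correlation of 0.2 to 0.5. With zero correlation there is no bias, and at r = −0.3 it runs from −0.06 to −0.19 SD for 10% to 40% excluded. No stated sample size or precision figure is affected, and neither are the feasibility outcomes, which are reported descriptively. The sentence needs correcting under either reading.

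**What to change.** Replace the phrase with a statement that the main efficacy analysis, and the week-12 goal attainment estimates taken to the definitive trial, include all randomised participants in the arm to which their occupational therapist was allocated, regardless of sessions attended, using all available outcome data. Keep a per-protocol or attendance-based analysis as supportive only, with its criteria defined in advance for both arms. If the authors meant as laid down in the protocol, delete the phrase and name the as-randomised set.

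The model sentence has to change as well. A conventional 2 × 4 mixed analysis of variance keeps only participants with all four assessments, so it would still drop anyone who missed one. A likelihood-based mixed model for repeated measures would retain them. Restricting the set to people with at least one post-baseline value should not be called intention to treat, since it leaves out randomised participants without follow-up; report their number by arm.

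The cost is two edited sentences and a possibly slightly smaller estimated effect. N stays at 120, and neither data collection nor trial conduct changes.

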**Methods:**

One hundred and twenty people with MS will be assigned to participate in either the COB-MS programme or a treatment as usual, wait-list control group as part of this single-blind, cluster-randomised controlled feasibility and preliminary efficacy trial of the COB-MS programme. The COB-MS group will participate in an eight-session occupational-based cognitive rehabilitation programme over 9 weeks. The primary outcome measure is the goal attainment scaling at 12 weeks. Participants will be assessed pre-intervention, post-intervention and at 12 weeks post-intervention and 6 months post-intervention. Qualitative evaluations of participants’ perspectives will also be examined as part of the feasibility study.

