**Discussion:**

Results will provide recommendations for a future definitive trial of COB-MS, with respect to both feasibility and preliminary, clinical efficacy. In the event that results indicate efficacy, study findings will suggest that COB-MS requires consideration as a means of enhancing cognitive and daily functioning in people living with MS.

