### Progression criteria

A traffic light system—green (go), amber (amend) and red (stop)—which allows for modification will be used [66], in consultation with the TSC. The key areas of risk are included in the criteria: trial recruitment, protocol adherence and outcomes. Criteria in the Acceptance Checklist for Clinical Effectiveness Pilot Trials (ACCEPT) [67] will also be used to evaluate progression. They will examine (1) feasibility and appropriateness of the trial design; (2) feasibility and appropriateness of the mechanics, management and safety of interventions; (3) acceptability and efficiency of implementing the research procedures. Trial components, exemplar monitoring methods and exemplar outcomes are included in the checklist. Transparent reporting will be made around the decision-making process for stopping, amending or proceeding to a main trial, as recommended by Avery et al. [66].

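### The named primary endpoint, goal attainment at 12 weeks, does not lead the preliminary efficacy analysis: a series of 2 × 4 ANOVAs treats it and ten secondary outcomes alike, so a chance signal is far likelier than 5%

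*Protocol article*

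**What the plan says.** The Abstract names one outcome and one time point: "The primary outcome measure is the goal attainment scaling at 12 weeks". The Primary outcome section repeats it: "The primary endpoint will be at the 12 weeks follow-up".

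The Secondary outcomes section then lists ten measures: SDMT, CVLT-II, TMT, BVMT-R, EMQ-R, EMQ-R Relative, GSES, Modified Fatigue Impact Scale, MSQOL-54 and GHQ-12. The relative-rated form is optional for participants.

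The Statistical analysis section fixes the efficacy method for all of them in one sentence: "Data resulting from primary and secondary outcome measures will be evaluated, per protocol, in terms of preliminary efficacy through a series of 2 (condition) × 4". The second factor is visit, and the rest of the sentence gives the method as "mixed (multivariate) analyses of variance as well as through correlational analysis". Just before this, goal attainment at week 12 is singled out, but only as a source of means and standard deviations for sizing a later trial.

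Two places could use the result. The Abstract's Discussion says that, if results indicate efficacy, "study findings will suggest that COB-MS requires consideration as a means of enhancing cognitive and daily functioning in people living with MS". The Progression criteria section lists the key areas of risk as "trial recruitment, protocol adherence and outcomes".

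**The concern.** The article names a primary endpoint but does not use it where efficacy is evaluated. Eleven outcomes enter the same series of analyses, no outcome leads, no contrast is named, and nothing is called exploratory.

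Each 2 × 4 analysis yields two effects that involve the arm: condition and condition × time. Neither is the 12-week difference. The condition effect averages the arm difference over all four visits, including the pre-intervention one. The interaction is a three-degree-of-freedom test that any pattern of divergence over time can trigger, in either direction.

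The Abstract's conditional conclusion covers cognitive as well as daily functioning. The cognitive tests and the memory questionnaire are all secondary, and no lead measure is named among them. A statement on cognition would therefore naturally draw on whichever of these measures came out positive. At stake is whether an efficacy indication from this trial can be told apart from chance when a definitive trial is considered.

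**Working it through.** **Inputs from the article.** Outcomes: 1 primary + 10 secondary = 11 (10 without the optional relative form). Visits: four (Design). Participants: 120 (Sample size). The article's own sizing is 90 × [1 + (8 − 1) × 0.05] = 121.5, which it takes as 121 and then as 15 × 8 = 120. It gives no false-positive rate for efficacy, so there is no figure of that kind to reproduce.

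**Assumptions, not in the article.** Two-sided 5% per test; no treatment effect on any outcome; within-person correlation 0.6; between-outcome correlation 0 to 0.5; no clustering, so that each test holds its nominal level. Ignoring therapist clustering is a separate matter and is kept out of these figures.

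**Step 1: why the omnibus tests miss the endpoint.** Let d1 to d4 be the arm differences at the four visits, with d3 at the 12-week follow-up. The condition effect is (d1 + d2 + d3 + d4)/4, so d3 has weight one quarter. If the programme shifts all three post-baseline visits by δ and d1 is 0, the condition effect estimates 3δ/4. The interaction tests d1 = d2 = d3 = d4 jointly and does not single out d3.

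**Step 2: independent outcomes, by formula.** P(at least one) = 1 − (1 − a)^k.

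- Either direction, both effects read (k = 22, a = 0.05): 1 − 0.95^22 = 67.6%.
- Either direction, one effect per outcome (k = 11): 1 − 0.95^11 = 43.1%. Without the relative form (k = 10) it is 40.1%.
- Favouring COB-MS, both effects (k = 22, a = 0.025): 1 − 0.975^22 = 42.7%.
- Favouring COB-MS, one effect per outcome (k = 11): 1 − 0.975^11 = 24.3%.
- For comparison, goal attainment alone with both effects read, either direction: 1 − 0.95^2 = 9.75%.

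**Step 3: correlated outcomes, by simulation** (120 participants, four visits, 11 outcomes). An interaction counts as favouring COB-MS when it is significant and the change from baseline to 12 weeks is better in the COB-MS arm.

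| What counts as a signal | Correlation 0 | Correlation 0.5 |
|---|---|---|
| Either direction, both effects | about 67% | about 51% |
| Either direction, interaction only | about 42% | about 29% |
| Favouring COB-MS, both effects | about 42% | about 30% |
| Favouring COB-MS, interaction only | about 24% | about 17% |

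Repeated simulations agree to within about three points. For example, the interaction-only figure in either direction at correlation 0.5 came out between 29% and 32%. The values at correlation 0 agree with the formulas in step 2.

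**The case against.** The case against has real force on several points.

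- **Ranking.** A reader might infer that the outcomes are unranked. The article does not support that: it names goal attainment at 12 weeks as primary and labels the rest secondary. What stands is narrower: the efficacy sentence does not use that ranking.
- **Size.** A reader might infer that an ineffective programme would show an efficacy signal more often than not. That holds only if both effects are read and a result against COB-MS also counts. An effect against the programme is not evidence for it, and once direction is required no reading examined exceeds one half.
- **Number of tests.** The article does not say which effect counts. Because the first visit is pre-intervention, condition × time is the more natural efficacy test, which gives the lower figures. The word multivariate may also mean that some outcomes are tested jointly, which would reduce the count, although a series still means several analyses.
- **Consequence.** The progression criteria state no p-value rule and are applied in consultation with the steering committee. The Abstract's sentence is conditional and says only that the programme requires consideration. That a chance finding would drive the decision is a possibility, not something the article says.
- **Scope.** This is a feasibility trial sized on retention, and multiplicity detail is commonly left to an analysis plan. That answers a complaint about a missing multiplicity rule. It does not answer the point here, which is that the stated method gives the named endpoint no leading role. The absence of an effectiveness sample size favours estimation with intervals over a series of tests read for efficacy.

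**Conclusion.** The concern holds in limited form. The article fixes an efficacy evaluation in which its own primary endpoint neither leads nor is isolated, while its conclusion reaches to cognition, where no lead measure is named.

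Under no treatment effect, the chance of at least one nominally significant effect favouring COB-MS is about 30–42% if both arm-related effects are read and about 17–24% if only the interaction is read. Counting either direction, the figures are about 51–67% and 29–42%. All are well above 5%. They rest on an assumed two-sided 5% level, separate tests for each of 11 outcomes, no clustering, and between-outcome correlation of 0 to 0.5. Stronger correlation or joint testing would lower them.

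**What to change.** In the Statistical analysis section, state that the preliminary efficacy reading rests on the arm difference in goal attainment scaling at the 12-week follow-up, reported with its 95% CI. State that the ten secondary measures are exploratory and will be reported as arm differences with 95% CIs and no significance claim. Limit the concluding sentence in the Abstract's Discussion to match. Naming one cognitive measure in advance as a key secondary is an option if a statement on cognition is wanted, but the correction does not depend on it.

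The cost is wording only, with no new data or participants. The small downside is that an isolated positive secondary result can no longer be presented as an indication of efficacy.
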